### Monitoring

#### Data monitoring

A data monitoring plan has been created and is available upon request. As both groups in this study are within the spectrum of regular care, no data safety monitoring board is installed. Furthermore, since this is a monocentre study, a coordinating centre is not needed. The CWZ Academy acts as a Trial Steering Committee in this study to provide independent oversight and yearly checks.

No interim analyses will be performed. As the treatments in both groups are within the range of usual care, we do not anticipate differences between the groups that could warrant early cessation of the study due to detrimental effects to the participant.

#### Adverse event reporting and harms

All AEs reported spontaneously by the subject, observed by the investigator, or his staff will be recorded. The patient’s general practitioner will receive a letter about the patient’s participation in the study. To prevent under registration of AEs, we will ask for this information during outpatient visits. AEs will be reported until 12 weeks for the PT group and 18 weeks for the surgery group.

Elective hospital admission will not be considered a serious adverse event (SAE). Prolongation of initial hospital stay after surgery due to pain or reduced mobility and the need for mobilisation under sedation (hardly ever performed after TTT) will not be considered a serious adverse event. The investigator will report all SAEs to the sponsor without any delay after obtaining knowledge of the events. The sponsor will report the SAEs through the web portal ToetsingOnline to the accredited METC, which approved the protocol within 7 days of first knowledge for SAEs that result in death or are life threatening, followed by a period of a maximum of 8 days to complete the initial preliminary report. All other SAEs will be reported within a maximum of 15 days after the sponsor has first knowledge of the serious adverse events. SAEs will be reported until 12 weeks for the PT group and 18 weeks for the surgery group.

#### Auditing

Monitoring will be performed once per year. It will involve monitoring the investigator site file, informed consent, SAEs, in- and exclusion criteria, among others. Monitoring will be performed according to Nederlandse Federatie van Universitair Medische Centra (NFU) guidelines and a monitoring plan by a monitor from the CWZ academy.

#### Protocol amendments

All amendments will be reported to the METC that gave a favourable opinion. Non-substantial amendments will not be notified to the accredited METC or the competent authority but will be recorded and filed by the investigator.

#### Dissemination plans

Overall trial results will be communicated to participants, presented at (inter)national conferences, and reported in peer-reviewed journals. There are no publication restrictions. Medically relevant incidental findings will be shared with the study subject.

## Discussion

The REVITALISE study is the first RCT to compare surgical intervention followed by PT to PT alone in patients with chronic PFP. This study’s results will gain insight into the most effective treatment for patients with chronic PFP and will enhance our treatment of this high burden disease with currently a high variability of provided care [14]. This variation seems to be not or weakly associated with patient characteristics, elucidating the need for a more standardised approach to prevent over- or under treatment. The study will answer the question whether patients receiving TTT followed by PT have less pain and better functional outcomes than those receiving PT alone. In addition to measuring the effectiveness of TTT plus PT versus PT alone, a range of other outcomes will be assessed (e.g., physical function, complications, direct medical costs), to provide a broader view of the effect of both treatments.

The strengths of the study include the randomised controlled design supported with multiple involved professions. Physiotherapists are involved in the design of the PT. Orthopaedic surgeons are involved in the TTT protocol. Since this is a single-centre study, little or no variation in surgical technique is expected.

This study has several limitations. First, the crossover design potentially affects long-term (i.e., > 12 weeks) comparisons of the groups, as well as induces bias in cases where patients become less motivated to follow physiotherapy. However, as the primary analysis is according to the intention-to-treat principles, we do not expect this to have a major impact. Second, at the time of presentation at the hospitals, patients will have had different treatments, i.e., the care given by the family physician, the outpatient physiotherapist, or other involved professionals. In our physiotherapy programme, special care is given to education of the patient about PFP, as well as a focus on building balance and strength in multiple muscle groups, not only the quadriceps. Third, for logistical reasons, it is not possible for all participants to receive physiotherapy from the same physiotherapist. To limit protocol variations, we will contact each physiotherapist to explain the research design, the PT, and the need to adhere to this programme. Simultaneously, the physiotherapist should tailor the programme to the participants, as their individual needs and limitations are always the highest priority.

The results of this study will address an important evidence gap and will have a significant impact on the care of patients with chronic PFP.

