#### TTT and PT versus PT only

The study involves four outpatient visits (at inclusion/randomisation, 6 weeks after the start of the intervention, after 12 (PT group)/18 weeks (surgery + PT group), and after 26 weeks in both groups). A physical examination will take place at every outpatient visit, with the addition of the decline step-down test (DSDT) at baseline and 12/18 weeks after randomisation. Patients will complete online questionnaires at every outpatient visit and 12 months after randomisation.

After randomisation, patients will either have a TTT (treatment group) or start with the PT (control group). From 12 weeks, there will be the possibility to crossover from the PT group to surgery if the symptoms do not improve. The criteria for this are a persisting high level of pain and patient-reported lack of effect of the PT. In that case, surgery will be performed within 2 weeks. Participants will then follow the same protocol as the TTT group, including the PT programme, surveys, and physical measurements.

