#### Secondary outcomes

Secondary outcomes are between-group difference in: pain during the intervention (VAS); functional outcomes (Kujala score, IKDC), activity level (Tegner score), quality of life (EQ-5D-5 L), and functional ROM (DSDT) at 12/18 weeks follow-up, as well as the change over time from baseline to 12 months follow-up. Furthermore, this study will provide a global overview of the direct medical costs of surgery + PT compared to PT only treatment.

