### Sample size

Our primary outcome is the between-group difference in overall knee pain 12 weeks after PT and 18 weeks after TTT and PT, measured with the VAS score. Our hypothesis is that the improvement in the TTT group will be greater than the improvement in the PT group.

To detect the superiority of the treat-to-target TTT with PT to PT alone, we calculated the required sample size for an independent samples t-test on the following assumptions: power (1-beta) 0.8, significance level (alpha) 0.05, and two-sided testing. Effect size was set at the MCID for VAS-pain, based on a study by Crossley et al., who demonstrated that a change in the VAS score of two points or more is considered clinically relevant and worthwhile for performing surgery [28]. Based on a study by Bayoumi et al., which compared different surgical techniques for patellar maltracking without instability, the anticipated mean for the PT only group was 6.2 (reflecting the pre-operative value), and SD was 2.0 [17]. Based on these parameters, a sample size of 16 patients per group is needed. Anticipating on a loss to follow-up of 20%, 20 patients per group are needed.

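### Intention-to-treat does not protect against crossover: endpoint timing shields the 12/18-week result, and later results compare strategies rather than TTT+PT with PT alone

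*Protocol article*

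**What the plan says.** In the protocol article:

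- **Discussion (limitations).** Crossover is named as a possible influence on comparisons beyond 12 weeks, and as a source of bias if patients put less into physiotherapy. The text then reassures: "as the primary analysis is according to the intention-to-treat principles, we do not expect this to have a major impact".
- **TTT and PT versus PT only.** From week 12, PT patients may have surgery if pain stays high and they report that PT is not working; the operation follows within 2 weeks. "Participants will then follow the same protocol as the TTT group, including the PT programme, surveys, and physical measurements". Both arms have a 26-week visit, and questionnaires are due 12 months after randomisation.
- **Primary outcome.** VAS pain is taken at week 12 in the PT arm and week 18 in the TTT arm. The section says that a later time was avoided because of crossover.
- **Secondary outcomes.** These cover the 12/18-week differences, "as well as the change over time from baseline to 12 months follow-up". The section on secondary endpoints analyses the longitudinal part with mixed models.
- **Methods for additional analyses.** A per-protocol analysis keeps only patients who did not cross over. A sub-analysis of the primary outcome adds adherence as a covariate.

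**The concern.** The Discussion raises two problems and answers both with ITT, which solves neither.

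First, ITT analyses patients in the arm to which they were randomised. A PT patient operated on after week 12 still counts as PT, so ITT carries the effect of crossover into the late estimates.

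Second, patients are told at recruitment that they may cross over (Patient recruitment). If this lowers effort in the PT programme, it acts before week 12 and can reach the primary endpoint. ITT leaves that in the result.

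At stake is how the late results are read. The Objectives section intends them for the national guideline, and the Discussion presents the trial as measuring TTT plus PT against PT alone. A small 12-month ITT difference could be taken as evidence that surgery adds little, when part of the PT arm has had the operation.

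**Working it through.** **1. The plan's own figures.** Inputs from Sample size: "we calculated the required sample size for an independent samples t-test on the following assumptions", "power (1-beta) 0.8, significance level (alpha) 0.05, and two-sided testing"; difference 2 cm ("a change in the VAS score of two points or more is considered clinically relevant"); SD 2.0 ("the anticipated mean for the PT only group was 6.2 (reflecting the pre-operative value), and SD was 2.0").

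n per group = 2 × (1.96 + 0.84)² × SD² / difference² = 2 × 7.85 × 4 / 4 = 15.7, so 16. This matches "a sample size of 16 patients per group is needed", and 16 / 0.8 = 20 reproduces the inflated size. An exact t-test calculation gives 16.7, so 17. With 16 evaluable per group, power is 80.7% (normal) or 78.1% (t). The sample size is not in dispute.

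**2. What protects the primary endpoint.** The last PT-arm measurement for this endpoint is in week 12. Crossover opens at week 12. Actual crossover therefore cannot enter the comparison, whichever analysis set is used. The protection comes from timing, as the Primary outcome section itself implies.

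**3. Week 26.** Assume that crossover is decided at week 12 and that week 26 counts from randomisation. Surgery falls at weeks 12–14. A splint phase of 4–6 weeks puts the start of PT at weeks 16–20. At week 26 these patients are 12–14 weeks after surgery (26 − 14 to 26 − 12) and 6–10 weeks into PT (26 − 20 to 26 − 16), so they have not finished the 12-week programme. The VAS section allows that recovery may still affect pain at week 18 of the TTT pathway. Recovery pain in crossovers would raise the PT-arm mean; early surgical benefit would lower it. The direction is open. No closing date for crossover is given, so later crossovers would be earlier in recovery, or not yet operated on.

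**4. Month 12.** Let c be the share of the PT arm that has crossed over. Assume a lasting true effect of 2 cm, gained in full by crossovers, and SD 2.0. Then

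ITT difference = 2 × (1 − c).

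The documents give no c, so a range is shown. Power is for a two-sided t-test at 0.05.

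| c | ITT difference (cm) | Power, 16 per arm | Power, 20 per arm |
|---|---|---|---|
| 0 | 2.0 | 78% | 87% |
| 10% | 1.8 | 69% | 79% |
| 20% | 1.6 | 59% | 69% |
| 30% | 1.4 | 48% | 58% |
| 50% | 1.0 | 28% | 34% |

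The 16-per-arm column is the planned evaluable number; the 20-per-arm column assumes no loss.

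**5. Does the per-protocol analysis repair this?** It removes PT patients selected for persisting pain. Suppose PT scores are normal with SD 2.0 and the worst 20% cross over. The mean of those left falls by SD × φ(z)/(1 − c), with z = 0.84 and φ(z) = 0.28: 2 × 0.28 / 0.8 = 0.70 cm. If the later score correlates 0.5 with the week-12 score, the shift is 0.35 cm. The remaining PT arm looks better through selection alone.

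**The case against.** The best defence is that the reassurance speaks of the primary analysis, and the primary endpoint was deliberately placed where crossover cannot reach it. On that reading the conclusion is right for actual crossover and only the reason is wrong. This stands for the 12/18-week result. It does not rescue the sentence, because the problem just named there is the comparison beyond 12 weeks, together with motivation.

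The protocol also discloses the long-term limitation and plans per-protocol and adherence analyses. The disclosure deserves credit, but an invalid reason then takes it back. The per-protocol analysis has the selection problem shown above. The adherence covariate is measured after randomisation and records sessions done, so it describes low motivation without removing its effect.

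Several stronger readings are tempting and not supported:

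- That crossover contaminates the primary endpoint. Actual crossover does not.
- That the trial is underpowered at 12 months against its own claim. The protocol makes no power claim for this secondary outcome, and the table uses a simple t-test where the plan uses a mixed model.
- That falling below the 2 cm threshold is itself telling. With the true effect set at exactly 2 cm, any crossover produces that.
- That crossovers lose their 26-week and 12-month measurements. The text says that they follow the TTT surveys; it does not say whether these replace the original ones or are added to them.

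**Conclusion.** The point holds in this form: the reason given in the Discussion is wrong, and it matters for what the late results can claim. The 12/18-week comparison is safe from actual crossover because of its timing, but ITT does not guard it against reduced motivation in the PT arm. The 26-week and 12-month ITT results estimate immediate TTT against PT with optional TTT from week 12. That is a legitimate strategy comparison, but a different question from TTT+PT versus PT alone.

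A reader might infer dilution at every late visit. It is probable at 12 months only; at 26 weeks the sign is unknown. The 12-month size rests on an assumed crossover share, full benefit in crossovers and a constant SD: 1.8 cm at 10% crossover down to 1.0 cm at 50%. The sample size and the primary model are unaffected. This is a correction that should be made, not a flaw in the main result.

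**What to change.** 1. In the Discussion, replace the ITT reassurance with the timing of the primary endpoint, for actual crossover only, and leave reduced motivation as an unresolved limitation.
2. Limit the claim about TTT+PT versus PT alone to the 12/18-week endpoint. Describe 26-week and 12-month ITT results as immediate TTT versus PT with optional TTT.
3. Report the number and timing of crossovers beside each late estimate.
4. State that crossovers complete the 26-week and 12-month questionnaires on the randomisation clock, in addition to any TTT-schedule surveys.
5. Add a sensitivity analysis that sets post-crossover values to missing and keeps the week-12 and weekly VAS in the model. State its missing-at-random assumption: given recorded pain, crossovers would have continued like PT patients with similar histories who stayed. Present the per-protocol analysis with its selection problem stated.

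None of this changes a treatment or the crossover rule. The cost is a narrower long-term claim, one extra analysis and a few extra online questionnaires per crossover patient. The added analysis will be imprecise in an arm of 20, and weak if nearly everyone with high week-12 pain crosses over.

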### Trial status

The study is currently open for inclusion. Recruitment started on 24 October 2023, and the expected end date of recruitment is 24 October 2025.

## Data Availability

Data will be handled according to FAIR principles. After completion of the study, metadata will be available upon request. For access to participant-level data and statistical code, an application can be submitted to the corresponding author. The PT used in the current study is available as supplementary material (see Supplementary file 1).

## Abbreviations

AE: Adverse event
AKPS: Anterior Knee Pain Score (Kujala score)
BMI: Body Mass Index
CI: Confidence Interval
CT: Computer Tomography (scan)
CWZ: Canisius Wilhelmina Ziekenhuis
DSDT: Decline step down test
EDC: Electronic data capture
EQ-5D-5L: Questionnaire for measuring health-related quality of life
GCP: Good Clinical Practise
IKDC: International Knee Documentation Committee Subjective Knee Form
iPFRN: International Patellofemoral Research Network
IQR: Interquartile range
MCID: Minimal clinically important difference
METC: Medical research ethics committee
in Dutch: Medisch-ethische toetsingscommissie
MMRM: Mixed model repeated measures
MPFFA: Maximum Pain-Free Flexion Angle
MRI: Magnetic Resonance Imaging (scan)
NFU: Nederlandse Federatie van Universitair Medische Centra
PFP: Patellofemoral Pain
PROMS: Patient Reported Outcome Measures
PT: Physiotherapy programme
QoL: Quality of Life
RCT: Randomised controlled trial
ROH: Removal of Hardware
ROM: Range of movement
SAE: Serious adverse event
SD: Standard deviation
TTT: Tibial Tubercle Transfer
TT-TG: Tibial tubercle trochlear groove
VAS: Visual analog scale
WMO: Medical Research Involving Human Subjects Act
In Dutch: Wet Medisch-wetenschappelijk Onderzoek
